### Dynamic contrast-enhanced magnetic resonance imaging examination

The subjects will receive DCE MRI on the study knee at baseline and 2 weeks after intervention using a 3.0 T scanner (Magnetom Tim Trio; Siemens Medical Solutions, Erlangen, Germany) with an eight-channel transmit-receive phased array knee coil (In vivo Corporation, Gainesville, FL, USA). The knee imaging protocol will consist of a sagittal three-dimensional high-resolution T1-weighted fast low angle shot sequence with selective water excitation (TR/TE = 500/20 ms; flip angle = 25; FOV = 18.0 cm; slice thickness = 3 mm; matrix = 320 × 240; receiver bandwidth = 200 Hz/pixel) as well as a sagittal T2-weighted fat-saturated spin echo (TR/TE = 4790/84 ms; FOV = 18.0 cm; slice thickness = 3 mm; matrix = 320 × 240; receiver bandwidth = 130 Hz/pixel). The synovial membrane will be evaluated using DCE sagittal three-dimensional T1-weighted fast low angle shot sequence with the following parameters: TR/TE = 12/3.9 ms, flip angle = 60; FOV = 15 × 15 cm, slice thickness = 5 mm, matrix = 256 × 128, receiver bandwidth = 200 Hz/pixel, temporal resolution = 30 seconds. This sequence will be acquired in contiguous 5-mm sagittal slices throughout the knee before, during and after intravenous bolus administration of double-dose contrast agent gadolinium diethylene triamine pentaacetic acid (0.2 mg/kg). Baseline pre-contrast static images as well as DCE images will be acquired after bolus injection [17,18]. The total acquisition time for the imaging protocol is 24 minutes.

Three-dimensional images of the knee joint will be rebuilt using a Leonardo workstation (Siemens Medical Solutions INC USA, [name]). The sagittal DCE sequence images and the intensity-time curve will be attained with the mean curve function. Four similar subchondral rectangular regions of interest (pixel area of 30) will be selected in the medial and lateral compartment of the distal femur and tibia plateau as well as the infra-patellar fat pad and supra-patellar fat pad. Measurement of these regions will be performed in terms of the enhanced rate and maximum upslope.

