### Statistical analysis

The data will be collected and analyzed according to the intention-to-treat principle. We will compare baseline characteristics in both groups. Efficacy analyses will be performed for both the intent-to-treat population and per-protocol population. The intent-to-treat population will consist of all randomized subjects who have been administered at least one treatment. In a per-protocol analysis, only patients who complete the entire clinical trial according to the protocol are counted in the final results. Primary outcome will be compared between both groups. The extent and time pattern of rescue medication will be reported in each randomized group; when comparing the underlying outcomes of the rescue medication, we assume the use of rescue medication varies with time, to allow for dependence within patients, so we adopt a multilevel regression approach with rescue as a time-dependent covariate [23]. Micro-perfusion alteration outcome will be compared using Student’s *t*-test. All statistical analyses will be performed using SAS 9.2 software (SAS Institute Inc, Cary, NC, USA). All statistical tests will be two-sided, and the level of significance will be set at 0.05.

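### Micro-perfusion is compared by a Student's t-test, which cannot adjust for the baseline scan; ANCOVA would be more precise, and one lead perfusion measure should be named

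*Protocol article*

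**What the plan says.** In the protocol article, Statistical analysis, the perfusion method is one sentence: "Micro-perfusion alteration outcome will be compared using Student"'s t-test. The threshold is common to every analysis: "All statistical tests will be two-sided, and the level of significance will be set at 0.05". No covariate, lead region, lead parameter or summary measure is named for perfusion.

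The section on dynamic contrast-enhanced MRI sets out the data. On timing: "The subjects will receive DCE MRI on the study knee at baseline and 2 weeks after intervention". On regions: "Four similar subchondral rectangular regions of interest (pixel area of 30) will be selected in the medial and lateral compartment of the distal femur" and the tibial plateau, "as well as the infra-patellar fat pad and supra-patellar fat pad". On parameters: "Measurement of these regions will be performed in terms of the enhanced rate and maximum upslope".

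Micro-perfusion is one of three secondary endpoints; the primary endpoint is VAS pain. The Discussion says that the imaging is meant to supply objective support for the lotion's effectiveness.

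**The concern.** There are two issues, of unequal weight.

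The first is precision. Each patient contributes a baseline scan, which is the natural predictor of that patient's follow-up scan. A two-sample t-test can use it only by subtraction, which fixes the baseline coefficient at 1, or not at all, which fixes it at 0. ANCOVA estimates the coefficient. The article names the t-test as its method, so this is a stated choice that can be improved and not a missing detail. The article also does not define alteration numerically, so the quantity to be tested is open.

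The second is multiplicity. Several perfusion measures come from the same knee, all tests share the 0.05 level, and none is given priority. Because the Discussion gives the imaging result evidential weight, an isolated significant region could be read as support for the treatment when it arose by chance.

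**Working it through.** **The plan's own figures.** The article gives no power, SD or error rate for perfusion, so there is no perfusion figure to reproduce. Its only design calculation is for VAS: 73 per group. This is recovered with a difference of 30 − 23 = 7 and an SD of 13 in both arms: 2 × (1.960 + 1.282)² × 13² / 7² ≈ 72.5, rounded up to 73. Nothing below depends on it.

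**Precision**

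Inputs: one baseline and one follow-up scan per patient (MRI section) and 1:1 randomization (Randomization and blinding). Assumptions, not in the article: equal SD σ at both scans, and a baseline to follow-up correlation r between 0.3 and 0.8.

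Outcome variance per patient that enters the group comparison:

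- t-test on follow-up only: σ²
- t-test on change: 2(1 − r)σ²
- ANCOVA: (1 − r²)σ², ignoring the one degree of freedom for the covariate

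Ratio of ANCOVA to change: (1 − r²) / [2(1 − r)] = (1 + r)/2. Ratio of ANCOVA to follow-up only: 1 − r².

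| r | Change, ×σ² | ANCOVA, ×σ² | ANCOVA ÷ change | ANCOVA ÷ follow-up only |
|---|---|---|---|---|
| 0.3 | 1.40 | 0.91 | 0.65 | 0.91 |
| 0.5 | 1.00 | 0.75 | 0.75 | 0.75 |
| 0.7 | 0.60 | 0.51 | 0.85 | 0.51 |
| 0.8 | 0.40 | 0.36 | 0.90 | 0.36 |

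Against change, the variance saving runs from 35% (r = 0.3) to 10% (r = 0.8). Against follow-up only, it runs from 9% to 64% over the same range. Confidence interval width goes with the square root: √0.65 = 0.81 and √0.90 = 0.95, so intervals are about 19% to 5% narrower than with change scores.

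**Multiplicity**

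Inputs: four subchondral regions plus two fat pads makes 6 regions; two parameters each gives 6 × 2 = 12 measures; two-sided 0.05 for each test. The assumption that each measure is tested separately is an inference from the text.

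If the 12 tests are independent and there is no true effect: 1 − 0.95¹² = 0.460.

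Independence is unrealistic for measures from one knee. A simulation of 12 equally correlated two-sided z-tests (400,000 draws) gave:

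| Common correlation (assumed) | Chance of at least one false positive |
|---|---|
| 0 (formula) | 46.0% |
| 0.3 | 39.7% |
| 0.5 | 31.9% |
| 0.7 | 23.1% |
| 0.9 | 13.5% |

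Smaller counts are possible. Pooling medial and lateral leaves 4 regions × 2 = 8 tests: 1 − 0.95⁸ = 33.7% if independent. Testing by tissue as the secondary endpoint is worded (fat pad, femur, tibia) leaves 3 × 2 = 6 tests: 1 − 0.95⁶ = 26.5% if independent.

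**The case against.** A t-test on change or on follow-up is valid and unbiased in a 1:1 randomized trial, so ANCOVA is a gain in efficiency and does not correct an error. That stands. So does the remark that the gain cannot be sized from the article, which gives no correlation between scans; over change scores it shrinks to 10% at r = 0.8. But under either reading of the t-test, and at every correlation considered, the gain is positive and costs no data.

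On multiplicity, the opposing case is stronger. Perfusion is a secondary outcome, this is a journal article, and adjustment among secondary measures is commonly left to a full protocol or analysis plan that is not shown. No rule says that one significant region will count as a perfusion effect. These points stand, and they are why this part comes second.

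Three stronger readings are tempting and are not supported:

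- A reader might infer that the baseline scan goes unused. The text does not say so; alteration between two scheduled scans most naturally means change, which does use it. What is absent is baseline as a covariate.
- A reader might infer that a chance finding is more likely than not. At the correlations tried, the probability is about 13% to 46%, always below one half.
- A reader might take 12 as a minimum number of tests. It is the count if every region and parameter is tested separately; the article does not state that, and 8 or 6 are possible.

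**Conclusion.** The point holds as a free improvement to a stated method, with a smaller recommendation attached. The t-test gives up precision that the baseline scan could provide: 10% to 35% of the variance if change is tested, 9% to 64% if follow-up alone is tested, for r from 0.8 to 0.3 and from 0.3 to 0.8 respectively, assuming equal SDs. The comparison is not invalid or biased.

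Without a lead measure, separate tests of all 12 measures at 0.05 would carry a 46% chance of at least one false positive under independence, and about 32%, 23% and 13% at common correlations of 0.5, 0.7 and 0.9. All are above 5%, but they rest on an inferred count and assumed correlations, and they matter only if a single significant region is used as evidence of effect. The weight that the Discussion puts on the imaging makes it worth closing off that possibility in advance.

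**What to change.** 1. Replace the t-test by ANCOVA for each perfusion measure: follow-up value as outcome, treatment group as factor, baseline value of the same measure as covariate; report the adjusted difference with its 95% confidence interval. This also settles what alteration means, because with baseline in the model the treatment estimate is the same whether follow-up or change is the outcome. It needs no further patients or scans, only new analysis wording.

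2. Before unblinding, name one lead perfusion measure: either one parameter in one region, or one parameter averaged over the four subchondral regions. Test that at 0.05. Report the others as exploratory with confidence intervals and no claim of significance, or with Holm adjustment (for 12 measures tested together the first step is 0.05/12 = 0.0042; with the lead tested apart, 0.05/11 = 0.0045 for the remaining 11).

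The cost of the second step is that fewer regions can be called significant. The VAS analysis and the sample size are unaffected.

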## Discussion

This study will provide clinical evidence on the efficacy of Jingui external lotion in treating KOA, and it will be the first randomized controlled trial to investigate micro-perfusion alteration of KOA with TCM external lotion using a DCE MRI technique. In TCM, KOA development is attributed to deficiency of the liver and kidney, and deficiency of qi and blood, attack of wind-cold-dampness evils, obstruction of channels and collaterals, qi and blood stagnation [24]. Thus, TCM that can promote blood circulation, remove blood stasis, and activate meridians to stop pain may be effective for KOA [13]. Fumigation and washing of TCM has recently been considered an inexpensive and convenient therapeutic approach for KOA [25]. Jingui external lotion is a classical and well-known external therapy in the orthopedic departments of TCM and has been demonstrated to provide a satisfactory effect for KOA in the clinic. Well-designed randomized controlled trials are needed to examine the efficacy of TCM treatments for OA.

It has been revealed that Chinese medicine promoting circulation and removing stasis could reduce intraosseous pressure [26]. Intraosseous hypertension has been reported to have an association with deep pain in patients with KOA [27]. To date, there is a lack of evidence to support the hypothesis that Chinese medicine promotes circulation; therefore, we will employ a DCE MRI technique to study micro-perfusion alteration, with the aim of attaining objective evidence of Jingui external lotion effectiveness in the treatment of patients with KOA.

## Trial status

Recruitment commenced in March 2014, and the trial is scheduled to end in March 2016.

## Abbreviations

DCE: dynamic contrast-enhanced
KOA: knee osteoarthritis
MRI: magnetic resonance imaging
OA: osteoarthritis
TCM: Traditional Chinese Medicine
VAS: visual analogue scale
WOMAC: Western Ontario and McMaster Universities Index
